**Methods:**

This study is a randomized controlled trial with parallel, three-group experimental arms. Eighty-one overweight/obese adults will be randomly allocated (1:1:1 ratio) to a vigorous exercise group, moderate exercise group or control group. The trial will be conducted at a military institution and the intervention groups will be submitted to exercise sessions in the evening, three times a week for 65 min, during a 2-week period. The primary outcome will be total spontaneous physical activity energy expenditure during a 2-week period. Secondary outcomes will be caloric intake, appetite sensations and laboratorial biomarkers. Intention-to-treat analysis will be performed using linear mixed-effects models to evaluate the effect of treatment-by-time interaction on primary and secondary outcomes. Data analysis will be performed using SAS 9.3 and statistical significance will be set at *p* < 0.05.

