### Sample size

Sample size was calculated based on a mean difference in daily energy expenditure between groups of 110 kcal [23], with a coefficient of variation equal to 1 (standard deviation of 110 kcal) [24]. The sample size required for the study, with an *α* of 0.05 (two-sided), *β* of 0.10 and estimating a drop out of 20%, is 81 adolescents (i.e., 27 in each group) [25].

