### Outcomes

The primary outcome will be total physical activity energy expenditure during the 2-week period. Secondary outcomes will be caloric intake, hungry and satiety sensations and biomarkers (lactate, cortisol, insulin, leptin, acylated ghrelin).

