### Data analysis

Descriptive analysis for variables of interest consist of means and standard deviation for continuous variables and percentage for categorical variables.

Energy expenditure associated with physical activity will be assessed in the first hour of accelerometer usage, corresponding to the period of the exercise sessions, and over the course of 15 days. Differences between sessions for energy expenditure in the first hour will be performed by using a one-way analysis of variance (ANOVA), followed by a post-hoc Scheffé test. Differences in daily and accumulated physical activity energy expenditure between groups will be performed using linear mixed models that take into account the correlations between repeated measures over time and dropouts. The models will assess the rate of change of the outcomes by the treatment-by-time interaction variable. The covariance structure of the models will be tested and residuals analyses will be performed. To deal with the potential weartime differences between groups, sensitivity analysis will be performed and a “non-wear time” variable will be created and included in the model. Data analysis will be performed using SAS 9.3 (SAS Institute Inc, Cary, NC, USA). Statistical significance will be set at *p* < 0.05 for all analyses.

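### Data analysis tests both daily and accumulated expenditure at p < 0.05 and does not tie the primary conclusion to the 2-week total that the protocol names as primary

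*Protocol article*

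**What the plan says.** The Outcomes section defines one primary outcome: "The primary outcome will be total physical activity energy expenditure during the 2-week period". The Abstract (Methods) agrees that it is a total: "The primary outcome will be total spontaneous physical activity energy expenditure during a 2-week period". The Sample size section works on the daily scale, with a "mean difference in daily energy expenditure between groups of 110 kcal", an SD of 110 kcal, two-sided alpha 0.05 and 90% power.

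The Data analysis section brings in two forms of the variable: "Differences in daily and accumulated physical activity energy expenditure between groups will be performed using linear mixed models". It gives the tested term for both: "The models will assess the rate of change of the outcomes by the treatment-by-time interaction variable". It then sets one threshold: "Statistical significance will be set at *p* < 0.05 for all analyses". The Abstract likewise says that the primary and secondary outcomes are evaluated by treatment-by-time interaction in mixed models. No sentence in Data analysis says which model answers the primary question, or that the other is supportive.

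**The concern.** A 2-week total is one number per participant and has no time axis, so a treatment-by-time interaction cannot be applied to it directly. The test has to use either the daily series or the running total, and the plan runs both. They ask different questions. The slope of the daily series contrasts late days with early days. The slope of the running total essentially measures the average level, which is what the primary outcome is about.

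Two things are at stake. The first is error control: two nearly unrelated tests, each at 0.05, with nothing to stop either from being presented as the primary result. The second is interpretation: if exercise lowers expenditure by a steady amount from the start, the daily rate-of-change test is blind to it, and the report could carry a null and a positive answer to one primary question with no stated rule for choosing between them.

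**Working it through.** **1. The plan's own figure.** Inputs from Sample size: difference 110, SD 110, two-sided alpha 0.05, power 0.90, dropout 20%.

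n = 2 × (1.960 + 1.282)² × (110/110)² = 21.01 per group. 21.01 / 0.80 = 26.3, so 27 per group and 81 in total. The stated size reproduces. It is a comparison of mean level between two groups, not of slopes.

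**2. Daily mean and total are the same test.** With 15 complete days, total = 15 × daily mean. The difference becomes 15 × 110 = 1,650 kcal and the SD 15 × 110 = 1,650 kcal, so the standardised difference is 1 on either scale. Sizing on a daily difference therefore does not conflict with a total as the outcome. Simulating both under no effect gave 4.5–5.1% rejection by either and no disagreement.

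**3. Daily slope and running-total slope are not the same test.** Take days s = 1 to 15 with mean 8 and Σ(s − 8)² = 280.

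- The daily slope weights day s by (s − 8)/280. The weights sum to 0.
- The running-total slope weights day s by (s − 1)(16 − s)/560. The weights sum to 1, so it is a weighted mean level.

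With independent days and no between-person variation, the two slopes correlate at 0.105. With between-person SD 0–110 kcal, day SD 75 or 150 kcal and AR(1) correlation 0–0.6, the correlation is 0.02–0.105. The running-total slope correlates at 0.91–0.997 with the 2-week total. The protocol gives only the SD of 110 kcal, so these variance components are assumptions.

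**4. False-positive rate if either result were claimed.** For independent tests, 1 − 0.95² = 9.75%. For correlated tests:

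| Correlation | Either test significant |
|---|---|
| 0 | 9.75% |
| 0.5 | 9.1% |
| 0.9 | 7.0% |
| 0.99 | 5.7% |
| 1 | 5.0% |

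Simulations used three groups of 22 over 15 days, per-person slopes and a 2-df test across groups, as a stand-in for the mixed models. They gave 8.9–9.8% (between-person SD 80, day SD 75; independent, AR(1) 0.5 or random-slope errors) and 9.5–10.6% (between-person SD 60 or 110, day SD 150, AR(1) 0.3 or 0.6). In the second set the single tests ran at 4.8–5.8%, so values above 9.75% are simulation scatter.

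**5. Behaviour when there is an effect in one arm.**

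- *Steady drop of 110 kcal/day from day 1.* Applying the daily weights gives −110 × Σ(s − 8)/280 = 0, so the daily slope rejects in about 5% of trials. The running-total weights give −110 × 1 = −110, and that test rejects in 76–99%. The two disagree in 75–95% of trials.
- *Drop growing linearly to a mean of 110 kcal/day.* The difference on day s is −110 × s/8, a slope of −13.75 kcal per day. Disagreement is 0.3–20%.
- *Growing drop with a mean of 55 kcal/day.* Disagreement is 35–55%, partly because power is low.
- *No effect.* Disagreement is about 10%.

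**The case against.** The strongest reply is that the protocol has already chosen. Abstract and Outcomes both name the 2-week total, and only the accumulated form corresponds to it. Daily expenditure is never called primary or co-primary. This stands: it would be wrong to say that the primary outcome is undefined. What is missing is the link from that outcome to one test in Data analysis.

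A reader might also infer that the primary false-positive rate is 10%. The documents do not support that. The figure needs a rule that success on either form counts, and a general threshold sentence is not such a rule. With the outcome as defined, the rate from this source is 5%; about 9.75% is the ceiling if the gap were used.

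A reader might further infer that the two analyses will usually disagree. That holds for a steady effect only. The Background hypothesis of a greater reduction after 15 days is at least as consistent with a developing effect, where the two largely agree unless power is low.

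The near-independence also depends on coding time as a linear slope. The rate-of-change wording points that way but does not fix it. With time categorical, under similar assumed variances, the two statistics correlate at about 0.93, either-test rejection is 5.7–6.7%, and disagreement under no effect is 2–3%. This limits the error-rate argument. It does not remove the blind spot: a constant difference between groups produces no treatment-by-time interaction in the daily series under any coding.

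Finally, labelling analyses as confirmatory or supportive is often left to an analysis plan that is not shown here. But the article does state two models, one tested term and one threshold, and one of those stated tests cannot detect a steady difference in the named outcome. That is more than omitted detail.

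**Conclusion.** The point holds in a limited form. The primary outcome is named, but Data analysis does not attach the primary conclusion to it and runs two treatment-by-time tests at an unadjusted 0.05. If time is a linear slope, the exposure is a primary false-positive rate between 5% and about 9.75%, the upper end only if either result were claimed. If daily is read as the daily average, or once the total is made decisive, the rate is 5%.

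The firmer part concerns the effect the trial was sized on. If that difference is steady, the daily test rejects at about its nominal 5% while the accumulated form usually finds it (76–99%, depending on assumed variances). How often the two conflict depends on the shape of the effect and should not be given as one expected figure. The simulations assume 22 completers per group, complete days, and per-person slopes in place of the planned mixed models.

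**What to change.** Add one or two sentences to Data analysis: the between-group comparison of the 2-week total, as defined in Outcomes (equivalently the mean daily level), is the single confirmatory analysis at two-sided 0.05; the daily treatment-by-time model is supportive and cannot by itself support a claim on the primary outcome.

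This keeps the primary error rate from this source at 5% and matches the quantity in the Sample size section, so 27 per group is unchanged. The alternative, testing both at 0.025, would need 25 rather than 22 completers per group. The cost of the proposed wording is small: a significant daily trend alone could no longer be reported as a positive primary result.

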Several physiological mechanisms, particularly hormonal, are involved in the energy expenditure and intake regulation and can explain these behavioral compensatory mechanisms [18, 19]. However, the existing interactions and the influence of physical exercise on these adjustments are still unclear. Therefore, it is necessary to better understand the relationship between physical exercise and energy expenditure, as well as the possible interdependence between energy expenditure and food consumption and the hormonal regulatory mechanisms related to energy balance in overweight individuals. The influence of different exercise intensities on energy expenditure and food intake should also be investigated. The EFECT study, which stands for “Physical Exercise and Compensatory Effects” in Portuguese, is designed to address this gap in the academic literature. For the main outcome, we hypothesize that a greater reduction on spontaneous physical activity energy expenditure will be observed in the vigorous exercise group (VEG) after the 15-day follow-up.

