#### Food consumption

Food and beverage consumption will be assessed by 24-h food recalls (REC24h). Nutritionists will conduct a face-to-face interview in four different moments during the intervention period: on the second and fifth days (Tuesday and Friday) in the first week; and at the 11th and 15th days (Thursday and Monday) in the second week. These days were selected to encompass weekdays (second, fifth, 11th) and weekend (15th), and days with (second, 11th) and without (fifth, 15th) exercise session.

During the interviews, each participant will be asked to report all food and beverages consumed (except water) on the previous day, including a description of food items, the amount consumed and the time of consumption. All items at each meal will be reviewed to ensure that no item is omitted, according to the menu at the restaurant. The 24-h recalls will be analyzed using the BrasilNutri software that encompasses a computerized food database developed for the 2008–2009 nationwide dietary survey [33].

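### For daily energy expenditure the named test is a treatment-by-time slope, which does not match the two-week total or the mean daily difference used for sizing, and the plan does not say whether the daily or the accumulated model is primary.

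*Protocol article*

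**What the plan says.** Outcomes section: "The primary outcome will be total physical activity energy expenditure during the 2-week period". Sample size section: "Sample size was calculated based on a mean difference in daily energy expenditure between groups of 110 kcal", with SD 110 kcal, two-sided alpha 0.05, beta 0.10 and 20% dropout, giving 27 per group and 81 in all.

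Data analysis section: "Differences in daily and accumulated physical activity energy expenditure between groups will be performed using linear mixed models", followed by "The models will assess the rate of change of the outcomes by the treatment-by-time interaction variable". The abstract likewise promises "linear mixed-effects models to evaluate the effect of treatment-by-time interaction on primary and secondary outcomes". Neither place names a group effect averaged over days as the test.

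Accelerometers are worn for 15 consecutive days, and the Data analysis section equates the first hour of wear with the exercise-session period. Diet recalls take place on four days within the intervention period, chosen to cover "days with (second, 11th) and without (fifth, 15th) exercise session". Biomarkers are sampled fasting in the morning of day 1, labelled baseline, and on day 15.

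**The concern.** A two-week total and a mean daily difference are levels; a rate of change is a slope. An interaction with time captures an intervention effect when a pre-treatment value anchors the time axis. For expenditure none is described, so in the daily model the interaction asks only whether the arms diverge between earlier and later intervention days. Compensation that begins with the first session and stays constant produces no divergence. Treating time as categorical does not help, because a constant shift still has zero interaction.

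At stake is the trial's main conclusion: a real compensation of the size planned for could be reported as absent. If it is uneven over the fortnight, the daily slope could even suggest a relative rise in spontaneous activity among exercisers.

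**Working it through.** **Inputs from the protocol.** Difference 110 kcal/day, SD 110, alpha 0.05 two-sided, power 90%, dropout 20%, 15 days of wear, sessions on Monday, Wednesday and Friday for two weeks. The recall schedule makes the second day a Tuesday, so day 1 is a Monday and sessions fall on days 1, 3, 5, 8, 10 and 12.

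**Assumptions not in the protocol.** Compound symmetry with within-person correlation 0.3 to 0.7; SD 110 read either as the SD of a 15-day mean or of a single day (the protocol does not say which); the time patterns below, each averaging −110 kcal/day.

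**1. The plan's own figure.** n = 2(1.960 + 1.282)² × (110/110)² = 21.01 per group. Then 21.01/0.8 = 26.27, so 27 per group and 81 in total. The stated size is reproduced as a two-sample comparison of means. Completers: 27 × 0.8 = 21.6, taken as 22.

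**2. Test of the mean difference.** If 110 is the SD of the 15-day mean, SE = 110 × √(2/22) = 33.2 and 110/33.2 = 3.32. Power = Φ(3.32 − 1.96) = 91% (90% with the t distribution). If 110 is a single-day SD, power is 97% to over 99%.

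**3. Slope of daily values.** The slope difference is Σ(t − 8)d(t)/280, where d(t) is the group difference on day t and 280 is the sum of squared day deviations.

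- Constant −110: Σ(t − 8) = 0, so the slope is 0.
- Session days only: −110 × 15/6 = −275 on each. Their deviations sum to −7 − 5 − 3 + 0 + 2 + 4 = −9, so the slope is −275 × (−9)/280 = +8.84.
- Day after each session: deviations sum to −3, so the slope is −275 × (−3)/280 = +2.95.

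For the SE, take correlation 0.3 and 110 as the SD of the mean. Total variance = 12,100/(0.3 + 0.7/15) = 34,904; within-person variance = 0.7 × 34,904 = 24,433; SE = √(2 × 24,433/(22 × 280)) = 2.82. This is the largest SE in the range considered.

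**4. Slope of a running total.** This slope is a weighted average of the d(t). The weights are zero on day 1, rise to 0.10 on days 8 and 9, fall to 0.025 on day 15, and sum to 1.

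| Pattern (mean −110) | Daily slope | Daily interaction rejects | Running-total slope |
|---|---|---|---|
| Constant | 0 | 5% (2.5% each side) | −110 |
| −165 fading to −55 | +7.9 | 80% to about 100%, wrong direction | −106 |
| −220 fading to 0 | +15.7 | about 100%, wrong direction | −102 |
| Session days only | +8.8 | 88% to about 100%, wrong direction | −110 |
| Day after session | +2.9 | 18% to 78%, wrong direction | −119 |
| 0 growing to −220 | −15.7 | about 100%, correct direction | −118 |

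Rejection rates use the normal approximation and span both readings of the SD. The running-total slope has 90–91% power for the constant pattern when 110 is the SD of the mean (97% to over 99% when it is a single-day SD), and 86–87% (95% to over 99%) for the −220 fade.

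**5. Intake.** Recalls refer to the previous day, so they cover days 1 (session), 4 (none), 10 (session) and 14 (Sunday, none). Deviations from their mean are −6.25, −3.25, 2.75 and 6.75, with sum of squares 102.75. The slope per unit of exercise-day effect is (−6.25 + 2.75)/102.75 = −0.0341. An assumed +200 kcal on exercise days would appear as −6.8 kcal/day per day. The protocol gives no SD for intake, so no rejection rate is attached.

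**The case against.** The strongest reply is that the plan does not model daily values alone. Accumulated expenditure is the quantity closest to the primary outcome, and the rate of change of a running total is essentially mean daily expenditure. A reader might infer that the primary test has no power for the sized effect; the documents do not support that, because the running-total interaction recovers it with the right sign in every pattern tried. This stands, and it narrows the point. It does not remove it: the plan does not say what form the accumulated outcome takes or which model is primary. If it is one total per person, no time interaction can be formed.

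A reader might also infer that the daily test will reverse the sign. That depends on patterns the documents do not supply. Sessions are at 5–7 p.m. and students go to their bedrooms at 10 p.m., so little of a session day follows exercise, and next-day compensation cuts the slope to +2.9. If day 1 fails the 10-hour wear rule, the session-day slope becomes −275 × (−4.5)/227.5 = +5.4. Growing compensation, which the hypothesis of a "greater reduction on spontaneous physical activity energy expenditure will be observed in the vigorous exercise group (VEG) after the 15-day follow-up" may envisage, is detected.

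Nor is it true that all data follow the start of exercise. Biomarkers have a day-1 fasting baseline, appetite is also rated before sessions, and the day-1 recall includes meals before the evening session.

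Finally, time coding and contrasts may be left to an analysis plan not shown. But naming the interaction as the tested effect is something the article states, in two places. The wording about differences between groups does not override it: with linear time and an interaction, the group coefficient is the difference at time zero, not the 15-day mean.

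**Conclusion.** The point holds for daily expenditure. The stated test is a slope, on data with no described pre-exercise anchor, while the outcome and the sizing concern a level. For an immediate, sustained −110 kcal/day the daily interaction rejects at chance (5%) against about 90% for the mean difference; this result needs no assumption about correlation. Opposite-sign slopes are possible under fading or session-day compensation, but only as assumed patterns.

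The accumulated model partly rescues the plan if it is a running total. Because neither model is designated primary, and the two can differ in sign on the same data, the main conclusion rests on a choice that the protocol leaves open. For intake, a linear time slope over the four recalls mixes time with exercise day and weekend. The sample size of 81 is not itself in error, and the interaction is suitable for the biomarkers. That expenditure has no baseline is inferred from the sentence on the first hour of wear.

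**What to change.** In the Data analysis section and the abstract:

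- **Expenditure.** Make the primary test the between-group difference in mean daily (or total) non-exercise expenditure over valid days, from a mixed model with day, or day type (session day, other weekday, weekend), as a factor. Keep treatment-by-time as a secondary description. State whether the daily or the accumulated outcome is primary, and what form the accumulated outcome takes.
- **Intake.** Test the group difference averaged over the four recalls, plus a group-by-exercise-day contrast, in place of a linear slope.
- **Biomarkers.** Keep treatment-by-time, since a true day-1 baseline exists.

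The cost is rewording and a few more degrees of freedom for day as a factor. Data, sample size and software are unchanged.

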## Monitoring

All adverse events that occur during the trial will be recorded and an independent committee will be consulted in case of severe adverse events to decide about the participants’ continuation in the trial.

## Discussion

Although physical exercise training has been widely recommended for the prevention and treatment of obesity [2], studies have demonstrated it is not an effective method of weight reduction [36, 37], probably due to compensatory changes, by reducing following non-exercise physical activity [10, 38] and/or increasing the energy intake [39]. However, other studies do not support this hypothesis and demonstrate that physical exercise, when prescribed and completed at a sufficient magnitude, is an effective method of weight reduction [40, 41]. Despite a large inter-individual variability in exercise-induced weight loss [42], people tend to lose less weight than is theoretically predicted [37].

A recent study in overweight adults showed that the effect of exercise training on the behavioral adaptive response was dose-dependent. Reduction of subsequent non-exercise physical activity occurred only in the group performing a high dose of exercise [43]. In addition, high-intensity exercise may change appetite-regulating hormones, leading to a greater suppression of orexigenic signals and greater stimulation of anorexigenic signals, contributing to a reduction in post-exercise energy intake, an effect known as ‘exercise-induced anorexia’ [18]. However, findings are not consistent and some other studies presented different results [44–47].

Therefore, the present study was designed to fill in this gap in the academic literature, investigating the effect of intensity of physical exercise training on subsequent non-exercise physical activity, appetite and energy intake as well as measuring possible physiological mechanisms underlying such compensatory phenomena. Highly controlled conditions for exercise and food intake in a free-living population is a hard task, which will be circumvented by studying a young military population living in the school. The results will help to understand this complex phenomenon and support the development of more effective interventions for the prevention and treatment of obesity.

This study protocol has some limitations: (1) although physical activity energy expenditure measurement is in accordance with others studies, bathing and other water-based activities will not be measured and this period will be considered as non-wear time; (2) within the first hour of waking up, cortisol increases and decreases dramatically and we may miss important changes in diurnal cortisol responses by only assessing salivary cortisol at one time point in the morning. However, as previously described, participants wake up at the same time and they will be instructed to collect the salivary sample at the same moment. In addition, the evaluation of changes in diurnal cortisol responses is beyond of the scope of the present study; and (3) the present study will use only overweight military men, making it difficult to extrapolate our results to other populations. Notwithstanding, we are investigating a complex phenomenon and a homogeneous sample seems to be more reasonable to answer our research question.

